## Abstract

**Background:**

Pregnant women with prior venous thromboembolism (VTE) are at risk of recurrence. Low molecular weight heparin (LWMH) reduces the risk of pregnancy-related VTE. LMWH prophylaxis is, however, inconvenient, uncomfortable, costly, medicalizes pregnancy, and may be associated with increased risks of obstetrical bleeding. Further, there is uncertainty in the estimates of both the baseline risk of pregnancy-related recurrent VTE and the effects of antepartum LMWH prophylaxis. The values and treatment preferences of pregnant women, crucial when making recommendations for prophylaxis, are currently unknown. The objective of this study is to address this gap in knowledge.

**Methods:**

We will perform a multi-center cross-sectional interview study in Canada, USA, Norway and Finland. The study population will consist of 100 women with a history of lower extremity deep vein thrombosis (DVT) or pulmonary embolism (PE), and who are either pregnant, planning pregnancy, or may in the future consider pregnancy (women between 18 and 45 years). We will exclude individuals who are on full dose anticoagulation or thromboprophylaxis, who have undergone surgical sterilization, or whose partners have undergone vasectomy. We will determine each participant's willingness to receive LMWH prophylaxis during pregnancy through direct choice exercises based on real life and hypothetical scenarios, preference-elicitation using a visual analog scale (“feeling thermometer”), and a probability trade-off exercise. The primary outcome will be the minimum reduction (threshold) in VTE risk at which women change from declining to accepting LMWH prophylaxis. We will explore possible determinants of this choice, including educational attainment, the characteristics of the women’s prior VTE, and prior experience with LMWH. We will determine the utilities that women place on the burden of LMWH prophylaxis, pregnancy-related DVT, pregnancy-related PE and pregnancy-related hemorrhage. We will generate a “personalized decision analysis” using participants’ utilities and their personalized risk of recurrent VTE as inputs to a decision analytic model. We will compare the personalized decision analysis to the participant’s stated choice.

**Discussion:**

The preferences of pregnant women at risk of VTE with respect to the use of antithrombotic therapy remain unexplored. This research will provide explicit, quantitative expressions of women's valuations of health states related to recurrent VTE and its prevention with LMWH. This information will be crucial for both guideline developers and for clinicians.

## Background

Pregnancy-associated venous thromboembolism (VTE), which may manifest as pulmonary embolism (PE) or deep vein thrombosis (DVT), is an important cause of maternal morbidity [1]. PE remains the leading cause of mortality in developed countries, accounting for approximately 30% of all maternal deaths [2-5].

Although cohort studies have consistently demonstrated that pregnant women with prior VTE are at increased risk of recurrence [6], they have varied considerably in their estimates of magnitude of risk [7-11]. In the largest prospective study of 125 pregnant women with a single previous episode of objectively diagnosed VTE in whom antepartum heparin was withheld [9], the incidence of antepartum recurrence was 2.4% (95% CI of 0.2 to 6.9%). In subsequently published large retrospective cohort studies, the probability of antepartum VTE in women not given antepartum prophylaxis was approximately 6% [12,13]. The inclusion of women with more than one prior episode of VTE as well as women with pregnancies ending in loss, and the failure to independently adjudicate recurrent events might account for the higher risk of recurrence observed in these retrospective studies. Despite the inconsistency, the overall risk of antepartum recurrent VTE in all studies was less than 10% and confidence intervals around the risk estimates of individual studies were overlapping.

The risk of recurrent VTE in the non-pregnant population is lowest among women whose thrombosis was provoked by a major transient risk factor, intermediate among those with an associated minor reversible risk factor, and highest among those whose thrombosis was provoked by a persistent risk factor or who had an unprovoked event [14-30]. Although thrombophilic abnormalities are risk factors for a first episode of VTE [19], these abnormalities do not appear to play an important role in the risk of recurrence [14,15,19,20,30-40]. Data regarding predictive factors for recurrent VTE during pregnancy are inconsistent and studies have not found a clear association between the presence or absence of transient risk factors or of a definable thrombophilia and the risk of recurrent VTE associated with pregnancy [12,13].

Providing thromboprophylaxis to those women at increased risk of thrombosis can potentially reduce pregnancy-related recurrent VTE. However, prophylaxis during pregnancy is problematic. Warfarin crosses the placenta and has the potential to cause teratogenicity and bleeding in the fetus [41-44]. Prophylactic LMWH does not cross the placenta [45] or increase the risk of serious adverse fetal outcomes [44-54], and does not appear to increase the risk of heparin-induced thrombocytopenia (<0.1%) or heparin-associated osteoporosis (<1%) [46,47,51,55-68]. However, prophylactic LMWH is expensive, inconvenient, uncomfortable to administer, may be associated with an increased risk of major obstetrical bleeding [46], and generally necessitates a planned delivery to permit epidural analgesia [46]. Additionally, women may perceive that LMWH creates an undesirable “medicalization” of their pregnancy.

A Cochrane systematic review [69] identified two randomized trials comparing heparin prophylaxis to placebo or no prophylaxis in pregnant women with prior VTE [11,70]. Both suffered from major methodological weaknesses including very small sample sizes. Current clinical guidelines are based primarily on the observational studies described above and indirect evidence suggesting that LMWH substantially decreases the risk of VTE by approximately 70% in a wide variety of clinical contexts [46,71].

In considering women’s choices of thromboprophylaxis during pregnancy, two considerations are of particular importance. First, treatment decisions during pregnancy have implications not only for the health of the mother, but also for the health of the fetus. Second, many women prefer to see pregnancy as a normal part of a healthy woman’s life, rather than as a medical condition. Additional considerations include the burden associated with the management: frequency and route of administration, pain, discomfort, and possible side effects of the medication, and the need, frequency and type of testing associated with a given regimen.

Given that the desirable consequences do not clearly outweigh the undesirable consequences of prophylaxis (or vice versa), the values and preferences of pregnant women should be taken into consideration when making management decisions. Because individuals have different attitudes toward risk, the uncertainty of estimates for both the baseline risk of recurrent VTE and the effects of thromboprophylaxis makes the consideration of individual preferences even more important.

There are two fundamental approaches to “patient-specific” decision-making: (1) a holistic direct choice procedure and (2) utility elicitation from individual patients followed by “patient-specific” decision analysis. The relative merit of these approaches is open to question and few studies have addressed this issue [72]. In the “direct choice” methods, participants are presented with relevant health states and the probabilities associated with occurrence of those health states under alternative management strategies. The most rigorous and widely used experimental direct choice method is the probability trade-off or probabilistic version of the threshold technique and it involves determining the threshold benefit at which patients accept a treatment with fixed undesirable consequences or the threshold toxicity or adverse effects at which patients will decline a treatment with fixed benefit [73,74]. Investigators can also use other simpler direct choice methods (e.g. decision board) that provide complementary information and can ensure understanding of the probability trade-off.

The second approach to decision-making involves decision analytic modeling using best estimates of the probability of occurrence of relevant health states under the management options being considered. Patients’ ratings of the disutility associated with relevant health states (typically on scales that range from death to full health) then inform the decision model and allow calculations of the quality adjusted life years associated with management options. There are a number of approaches available for eliciting health state evaluations [75]. The standard gamble approach is most consistent with utility theory and is generally preferred by health economists [76,77]. Although the visual analog scale is theoretically less satisfactory than the standard gamble, it is much easier to understand, takes far less time to administer, and has superior psychometric measurement properties than to the standard gamble [78-82].

In atrial fibrillation [83,84], and to a lesser extent in VTE and thrombolytic therapy for stroke [85], investigators have studied patients' values and preferences. A recently completed systematic review of patient preferences for antithrombotic treatment did not identify any studies of pregnant women [86]. The objective of this study is to address this gap in knowledge.

## Methods

We will perform a multi-center international cross-sectional interview study at six centers in four countries: two in Hamilton, Ontario, Canada; one in Buffalo, USA; one in Oslo, Norway; and two in Helsinki, Finland.

### Study population and eligibility criteria

Pregnant women with a history of lower extremity DVT or PE who are considering thromboprophylaxis to prevent recurrent antepartum VTE constitute the ideal patient population. However, only a small number of such women are expected to present at the six centers over the time frame of the study. Therefore, we will also include women with a history of lower extremity DVT or PE who are planning pregnancy, and women who are 18 to 45 years of age with a history of lower extremity DVT or PE and may at some point be planning a future pregnancy. We will exclude women who are currently receiving thromboprophylaxis or full-dose anticoagulation, have undergone surgical sterilization (tubal ligation or hysterectomy), have a partner who has had a vasectomy, and those unwilling or unable to provide informed consent.

### Recruitment strategy

We will prospectively identify women who are currently pregnant or planning a pregnancy as they are referred for counseling, and identify women with a history of VTE with the potential to become pregnant by reviewing patient files. We will approach women referred for consideration of thromboprophylaxis prior to their consultation and will make initial contact with women who are not currently pregnant or planning a pregnancy by letter and then by telephone.

### Study maneuvers

A member of the research team will meet with women who express an interest in participating, and will explain the purpose of the study and carry out the informed consent process. If patients decline to participate, we will collect the reason for refusal. If patient consent to the study, we will make arrangements for interviews. We will use standardized scripts developed by the research team to ensure a standard approach across centres and interviewers. Expert and non-expert clinicians and allied health professionals have reviewed and revised the scripts to ensure understandability and readability by a lay person with a grade 9 reading level.

#### The participant interview

Figure 1 presents the flow of the interview. We will determine patients' age, educational attainment, and current pregnancy status, as well as specific details about their past venous thromboembolic events (including occurrence of PE or DVT, number of events, date of the last event, presence or absence of precipitating risk factors prior to their event [Table 1]), known hypercoagulable states (Table 1), family history of VTE, type and duration of treatment for their event(s), adverse treatment effects, completeness of their recovery (for example, presence or absence of residual chest pain or shortness of breath, and/or residual leg swelling, pain or discoloration), and presence or absence of prior experience with injection of prophylactic doses of LMWH during pregnancy.

**Figure 1 F1:**
[figure not shown]
Interview flow chart.

**Table 1 T1:** Potential precipitating risk factors assessed regarding the past venous thromboembolic event Minor transient (i.e. now resolved) risk factors within 8 weeks of initial VTE

**Minor transient (i.e. now resolved) risk factors within 8 weeks of initial VTE**	**Major transient (i.e. now resolved) risk factors within 8 weeks of initial VTE**	**Known hypercoagulable state**
Pregnancy	Leg casting	Deficiency of antithrombin, protein C, or protein S
Postpartum (defined as 6 weeks after delivery)	Major surgery (>30 minutes; general or spinal anesthesia)	Activated protein C resistance/factor V Leiden
Hormonal contraception (birth control pill, patch or needle)	Acute medical illness with hospital admission for ≥ 3 days	Prothrombin gene mutation
Airplane travel (longer than 6 hours)	Immobilization ≥ 3 days (in bed except to go to washroom)	Anticardiolipin antibody positivity
	Active cancer	Nonspecific inhibitor

#### Direct choice exercises

We will determine each participant’s willingness to receive LMWH prophylaxis through direct choice exercises. Women will initially complete what we refer to as the real-life scenario, followed in order by hypothetical scenarios, the visual analog scale, the probability trade-off exercise, a review of their answers, and finally questions to examine their understanding their understanding of the scenarios. Use of decision boards will facilitate patient understanding of the direct choice exercises. Descriptions of each phase of the interview follow.

##### Real life scenario

We will initially present each woman with a decision board that will include the probabilities of developing VTE during pregnancy given the characteristics of her prior VTE (see below). This scenario will contain information similar to that received during standard clinical care but presented in a more systematic manner than that is typical in clinical practice.

For this real life exercise, we will have two potential scenarios. We will classify women as low or high risk of recurrence. We define low risk of recurrence as the absence of a known thrombophilia and prior VTE associated with a major transient risk factor within 8 weeks prior to their last event, and higher risk of recurrence as prior unprovoked VTE, VTE associated with a minor transient risk factor within 8 weeks prior to the event or any VTE in association with a known hypercoagulable state. (Table 1) We estimate that the risk of antepartum recurrence for women judged to be at lower risk lies between 0 and 5%, while that for higher risk women ranges between 5 and 10%. We will assume that prophylactic LMWH reduces the risk of antepartum recurrence by approximately 70% [71]. To ensure optimal understanding, we will present the risk of recurrence with and without LMWH prophylaxis in three different ways: table, bar chart and pictograph (Table 2 and Figures 2 and 3). 

**Table 2 T2:** Example of table presenting the risk of antepartum VTE recurrence for women considered at high risk of recurrent VTE during pregnancy

	**Without low molecular weight heparin use**	**With low molecular weight heparin use**
Probability of developing a blood clot during your pregnancy	5-10 in 100	1-3 in 100
Probability of NOT developing a blood clot during pregnancy	90-95 in 100	97-99 in 100

**Figure 2 F2:**
[figure not shown]
Example of bar chart presentation for women considered at high risk of recurrent VTE during pregnancy.

**Figure 3 F3:**
[figure not shown]
Example of pictogram presentation for women considered at high risk of recurrent VTE during pregnancy.

For the VTE health state, we will instruct women to consider their previous venous thromboembolic event. Women with more than one event will consider their most recent episode. We will instruct women with previous experience in the use of prophylactic LMWH for longer than 2 weeks during pregnancy to consider their previous experience when making a decision. We have prepared a description of the experience of LMWH use throughout pregnancy for women without experience in the use of LMWH prophylaxis during pregnancy (Additional file 1: Appendix 1). To ensure clinical verisimilitude, clinicians with considerable experience in the use of LMWH in pregnant women prepared the description and experts in obstetrics and thromboembolism reviewed them.

After reviewing this information, we will ask participants to decide whether or not they are willing to take LMWH during their pregnancy (for those who are pregnant) or whether they would be willing to do so in a subsequent pregnancy. Women currently pregnant and those referred for consideration of prophylaxis with a future pregnancy will meet with their health care provider and may wish to discuss the information provided with other people (for example, family members, friends, family physician, midwife or obstetrician). We will record the final decision after these additional consultations.

##### Hypothetical scenarios

We will provide study participants with three standardized scenarios in which the baseline risk of recurrent VTE, with and without the use of LMWH (assuming a 70% relative risk reduction) [71], will be varied (Table 3). Interviewers will show each woman a decision board with pictograms representing a low, followed by a medium, then a high risk of recurrent VTE. Participants will express their willingness to use LMWH given the associated burden (either based on their own prior experience or the standardized description [Additional file 1: Appendix I]), and the absolute magnitude of VTE risk reduction associated with the varying VTE recurrence risks. 

**Table 3 T3:** Hypothetical scenarios with variable baseline risks of recurrent VTE and estimates of LMWH effectiveness

	**Risk of recurrence**		
	**Low risk**	**Medium risk**	**High risk**
Without LMWH	4 in 100	10 in 100	16 in 100
	(96 in 100 will not)	(10 in 100 will not)	(84 in 100 will not)
With LMWH	1 in 100	3 in 100	5 in 100
	(99 in 100 will not)	(97 in 100 will not)	(95 in 100 will not)

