### Outcomes

The primary outcome measure will be the minimum threshold reduction in VTE risk in the probability trade-off exercise at which women switch from declining to accepting LMWH prophylaxis (which we will refer to as the “VTE threshold”).

Secondary outcomes will include:

(i) women’s willingness to take prophylactic LMWH according to their classification as either high or low risk for recurrence,

(ii) women’s willingness to take prophylactic LMWH for each of the three hypothetical scenarios

(iii) Utilities for each of the five health states assessed in the FT (the burden of prophylactic LMWH use during pregnancy – either the standardized experience or the patient’s prior experience-, a pregnancy with the participant’s own most recent VTE, a standardized description of pregnancy-related DVT, a standardized description of pregnancy-related PE, and a standardized description of an obstetrical bleed [Additional file 1: Appendix I]).

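### Table 3 misstates the medium-risk scenario: beside a VTE risk of 10 in 100 without LMWH, the no-event count is printed as 10 instead of 90, and the study boards should be checked against the corrected value

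*Protocol article*

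**What the plan says.** The section on hypothetical scenarios gives three standardized risk levels, refers to Table 3 for their values, and derives the with-LMWH risks by "assuming a 70% relative risk reduction". On delivery it states: "Interviewers will show each woman a decision board with pictograms representing a low, followed by a medium, then a high risk of recurrent VTE". It then says: "Participants will express their willingness to use LMWH given the associated burden", together with the absolute size of the risk reduction.

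Table 3 pairs each risk with its no-event count. Without LMWH, the low-risk column has 4 in 100 with "96 in 100 will not", and the high-risk column has 16 in 100 with "84 in 100 will not". The medium-risk column has 10 in 100 with "10 in 100 will not". With LMWH, the medium-risk column has 3 in 100 with "97 in 100 will not".

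Under Outcomes, secondary outcome (ii) is women's "willingness to take prophylactic LMWH for each of the three hypothetical scenarios". The Analysis section models those choices by hierarchical logistic regression, with the absolute risk reduction (high, moderate, low) as the first-level variable.

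**The concern.** Each pair in Table 3 describes the same 100 women, split into those who have a VTE and those who do not. One pair fails that requirement by a wide margin.

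This is more than a slip in background text, because the article points to Table 3 for the content of a study stimulus. A board or script built from the table as printed would give a woman two incompatible descriptions of her medium-risk baseline. On the no-event line, LMWH would seem to do far more at medium risk than at high risk. The scenario exercise relies on a benefit that rises from low to medium to high, and its analysis is coded that way. Answers to a faulty medium board would not measure willingness at the intended benefit.

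**Working it through.** **Inputs.** All six risk and no-event pairs come from Table 3. The 70% relative risk reduction comes from the text that introduces it. Table 2, in the section on the real life scenario, serves as a cross-check.

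**Step 1: complement check.** Risk plus no-event count should equal 100.

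| Scenario | Without LMWH | Sum | With LMWH | Sum |
|---|---|---|---|---|
| Low | 4 + 96 | 100 | 1 + 99 | 100 |
| Medium | 10 + 10 | **20** | 3 + 97 | 100 |
| High | 16 + 84 | 100 | 5 + 95 | 100 |

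Five of the six pairs reproduce. The medium pair without LMWH falls short by 100 − 20 = 80.

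**Step 2: which of the two numbers is wrong.** With-LMWH risk = baseline risk × (1 − 0.70).

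- Low: 4 × 0.30 = 1.2, printed as 1.
- Medium: 10 × 0.30 = 3.0, printed as 3.
- High: 16 × 0.30 = 4.8, printed as 5.

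The printed risks agree with the 70% assumption to the nearest whole event. If the no-event count of 10 were right instead, the baseline risk would be 100 − 10 = 90, and a 70% reduction would leave 90 × 0.30 = 27, not 3. The risk of 10 is therefore sound, and the no-event count must be 100 − 10 = 90.

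**Step 3: cross-check.** Table 2 gives a risk of 5 to 10 in 100 without LMWH and a no-event count of 90 to 95 in 100. There, a risk of 10 is paired with 90.

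**Step 4: size of the distortion, if it were shown to a participant.** The gain from LMWH can be read from either line of a scenario.

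| Scenario | Gain from event line | Gain from no-event line as printed | Gain from no-event line corrected |
|---|---|---|---|
| Low | 4 − 1 = 3 | 99 − 96 = 3 | 3 |
| Medium | 10 − 3 = 7 | 97 − 10 = **87** | 97 − 90 = 7 |
| High | 16 − 5 = 11 | 95 − 84 = 11 | 11 |

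As printed, the no-event gains run 3, 87, 11. Corrected, they run 3, 7, 11 and agree with the event line throughout.

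**Step 5: where the cell could and could not reach.**

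- *Secondary outcome (ii) and the hierarchical logistic regression.* The coding of the absolute risk reduction is unaffected. Only the medium-scenario answers could be, and only if the board or script is wrong.
- *Consistency check.* Interviewers review answers across the exercises. A medium answer given to a faulty board could look inconsistent with the rest.
- *Primary outcome.* The trade-off exercise fixes the risk without prophylaxis at 16 in 100 and varies the risk with LMWH. This cell is not part of it.
- *Decision model.* Its inputs are the woman's utilities from the feeling thermometer and the VTE risks. The Analysis section compares its results with the VTE threshold. The no-event count is not an input.

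**The case against.** The strongest reply is that this is a typing error in a journal article and nothing more. The wrong value repeats the 10 from the cell above it, the other five pairs are right, and the intended value is not in doubt. Table 3 is captioned as a list of scenarios, not as a reproduction of a board. The article says that clinicians and allied health professionals reviewed the scripts and that the scripts were pilot-tested, which makes it less likely that such an error survived into the interview materials. Even on a faulty board the event counts, 10 falling to 3, would be correct, and the review of answers gives each woman a chance to revise.

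Most of this stands. A reader might infer from Table 3 that participants see the wrong figure and that the medium scenario is already compromised. The documents do not support that: the boards, pictograms and scenario script are not shown, and a slip confined to the article is the likelier explanation. A reader might also infer harm to the decision analysis or the primary outcome. Neither uses this cell. The Abstract speaks loosely of comparing the decision analysis with a woman's stated choice, but the Analysis section names the VTE threshold as the comparator.

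What the reply does not remove is the error itself, or the reason to check. Script review and pilot testing make a correct board probable but do not show it, and Table 3 is the only specification of these scenarios in the article.

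**Conclusion.** The arithmetic error is certain and follows from the table alone: the medium-risk no-event count without LMWH is 90 in 100, not 10.

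Its effect on the study is conditional. If the materials already show 90, the matter ends with a correction to the article. If the medium-risk board or script carries the printed value, the apparent no-event gain is 87 per 100 instead of 7, and one of the three scenario results in secondary outcome (ii) is affected, with the regression that uses those answers.

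An indirect route to the primary analysis exists, but it needs several further steps. The board would have to be wrong, it would have to produce inconsistencies that women leave uncorrected, and results would have to differ between consistent and inconsistent responders, because only then does the plan restrict the primary analysis to consistent responders. Nothing in the article shows that any of these holds.

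Severity is minor to moderate: minor as a printed slip, moderate only because Table 3 specifies a stimulus.

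**What to change.** 1. Correct the medium-risk cell without LMWH in Table 3 to 90 in 100.
2. Confirm that the medium-risk board, pictogram and script at all six centers show 90, and record that the check was made.
3. Only if a woman is found to have been shown the wrong figure, flag her medium-scenario answer and set it aside in the scenario analysis. Keep her low- and high-risk answers and her trade-off result. The flag also lets the consistency review recognize a discrepancy that arises solely from the faulty board.

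The cost is a one-cell correction and a short check of materials. No design, sample-size or primary-analysis change is needed, and no data are lost unless step 2 finds an actual exposure.
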